Interventions such as antibiotic stewardship programmes, education and training initiatives targeted at prescribers and patients, financial incentives, among others have been implemented in England to reduce AMR through reduced prescribing. In particular, the Quality Premium (QP) is a National Health Service (NHS) England initiative established in 2013 to reward Clinical Commissioning Groups (CCGs) financially based on the quality of specific health services considered to be of national or local priority and commissioned over a specific period.^17^ Improvement of antibiotic prescribing in primary care was one of the national priorities in the 2015/2016 guidance,^18^ constituting 10% of the premium awarded from 2016/2017 to date.^19 20^ Key aspects of the ‘improved antibiotic prescribing’ priority are reductions in the number of antibiotics prescribed in primary care facilities across England and in the proportion of broad-spectrum antibiotics prescribed in primary care (2015–2017).^19^ Part of the requirements in the 2015/2016 QP guidance for demonstrating improved antibiotic prescribing by CCGs was a reduction in the number of antibiotics prescribed in primary care by 1% of the mean value in England in 2013/2014 (ie, 1.61 items per Specific Therapeutic group Age-sex Related Prescribing Unit (STAR-PU)). This was further increased to 4% in the 2016/2017 guidance.

Emerging evidence suggests a reduction in antibiotic prescribing in primary care practices in the UK following the QP initiative.^21 22^ Prescribing data from England show a reduction of about 2.7 million antibiotic items between 2014/2015 and 2016/2017 financial year.^23^ Eighty-eight per cent of the CCGs in England achieved the target of reducing antibiotic prescribing in the first 2 years of QP.^21^ Also, there has been a significant reduction in the proportion of broad-spectrum antibiotics prescription with 83% of the CCGs meeting their target in the first 2 years.^21^ Such reductions in antibiotic prescribing would be expected to contribute to reductions in the development of resistance.^24^ However, little is known about the mechanisms by which the QP initiative impacted on antibiotic prescribing in primary care practices.

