### Variables

The predictor will be a binary variable indicating the implementation of the QP intervention. The intervention will include all periods after March 2015 when the 2015/2016 QP guidance in England was published, while the control will be periods prior to this. The primary outcome of interest is the rates of antibiotic prescribing at CCG level in England, which will be a continuous variable indicating the number of items (per STAR-PU) prescribed per month.

To account for differences in practice and CCG characteristics that can contribute to variance in antibiotic prescribing, we will be adjusting for the number of general practitioners in each practice (from the NHS Workforce data),^35^ the index of multiple deprivation (from the Department for Communities and Local Government),^36^ prevalence of comorbidities (asthma, chronic obstructive pulmonary disease, diabetes, cancer, chronic kidney disease (from the NHS Quality and Outcomes Framework database)),^37^ the prescribing rate of other non-antibiotic drugs (opioids and benzodiazepines) and seasonal influenza vaccination rate (from PHE).^38^

Mediator variables will be derived from the questionnaire data from a PHE survey,^39^ with 187 of the 209 AMS leads representing CCGs in England and data from other organisations that have evaluated the interventions treated as potential mediators in this study. In the PHE survey, participants were required to complete questionnaire items, which included their adoption of national and local strategies in their respective CCG to enable them to meet QP targets on antibiotic prescribing in primary care. The mediator variables will be binary or continuous variables, indicating the adoption of key interventions and intermediaries that are hypothesised to reflect in the integration of the QP guidance in improving antibiotic prescribing in primary care practices.

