### Statistical analysis

Our first analysis will be an interrupted time series to investigate whether antibiotic prescribing rate in England has changed over time, and how such changes, if any, are associated with the QP implementation in March 2015. This will be conducted using the ordinary least square regression method^41^ to assess whether the 2015/2016 QP establishment resulted in a shift in the level and trend in antibiotic prescribing in primary care in England compared with the period before the intervention. Using the practice-level dataset, a univariate time series with the mean antibiotic items (STAR-PU weighted) prescribed in all primary care practices in England for each month will be conducted using the *ITSA* function on Stata, with post-trend specification to show a postintervention trend. The Cumby-Huizinga general test for autocorrelation will be used for general specification test of serial correlation in the time series data.^42^

A new QP guideline was implemented each financial year with changes in the prescribing rate target and the proportion that improved prescribing constituted in the QP award for each year. Our mediation analyses will investigate the effects of the QP by comparing antibiotic prescribing rate in the financial year before its implementation to each subsequent year postimplementation; as such, our dataset for the mediation analyses will have the control group as the financial year before QP and the intervention group as a specific post-QP implementation year. Three analyses will be conducted for each of the three financial years since QP establishment. This will enable us to compare the effects of the different target levels that have been set over the years and the proportions of the QP award attributed to improvement in antibiotic prescribing.

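### The 2016/17 and 2017/18 contrasts with the pre-QP year are cumulative, so they cannot compare the effects of the yearly targets or award shares as the article claims

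*Protocol article*

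**What the plan says.** Under Statistical analysis, the Protocol article plans mediation analyses by "comparing antibiotic prescribing rate in the financial year before its implementation to each subsequent year postimplementation". The dataset for each has "the control group as the financial year before QP and the intervention group as a specific post-QP implementation year". It adds: "Three analyses will be conducted for each of the three financial years since QP establishment". The stated purpose is: "This will enable us to compare the effects of the different target levels that have been set over the years", and the sentence goes on to claim the same for the share of the QP award tied to prescribing. The reason given for going year by year is that "A new QP guideline was implemented each financial year with changes in the prescribing rate target", and the article says there that the award share changed too.

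Under Variables, the predictor is a binary indicator of QP implementation: "The intervention will include all periods after March 2015 when the 2015/2016 QP guidance in England was published". It has no level for target, award share or years already spent under QP.

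The Introduction gives the 2015/16 target as a 1% reduction relative to the 2013/14 England mean of 1.61 items per STAR-PU, then: "This was further increased to 4% in the 2016/2017 guidance". It describes the prescribing priority as "constituting 10% of the premium awarded from 2016/2017 to date". It gives neither a numerical target for 2017/18 nor a separate share for 2015/16.

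**The concern.** Apart from mergers, the same CCGs pass through all the targets in the same order, with no break in QP. A CCG observed in 2016/17 has already had one year of QP, and in 2017/18 it has had two. Any effect of the first year that is still present is part of the later contrasts.

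The article therefore attributes to target level something that also reflects length of exposure. A steady fall under any sequence of targets would make the later contrasts larger, and a reader following the stated purpose would take this as evidence that the higher target worked better. Because each year's target applies nationally, no CCGs face a different target in the same year, so target level is tied to calendar year. The award-share claim has the same weakness, and the article's two statements on share disagree.

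**Working it through.** The article gives no figure to reproduce here. The question is what the planned contrasts identify.

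**Inputs from the article.** One pre-QP control year and three post-QP years (Statistical analysis). QP continuous after March 2015 and a binary exposure (Variables). Targets of 1% and then 4%, and a baseline of 1.61 for the first (Introduction). The control year is not named; 2014/15 follows from the March 2015 start.

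**Assumed inputs.** The own effect of year j's guidance, e_j, in % of the baseline rate; the fraction r of an effect that persists from one year to the next; and a secular trend t in % per year. The article gives none of these, so a range is shown.

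**Formula.** The contrast of post-QP year k with the pre-QP year is

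C_k = k·t + Σ(j ≤ k) r^(k−j)·e_j

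which gives

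- C_1 = t + e_1
- C_2 = 2t + r·e_1 + e_2
- C_3 = 3t + r²·e_1 + r·e_2 + e_3

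C_1 contains no earlier antibiotic QP year. C_2 and C_3 do. Barring chance cancellation, all three equal the yearly effects only when r = 0 and t = 0.

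**Results (C_1, C_2, C_3 in %).**

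| Own effects | r | t | Contrasts |
|---|---|---|---|
| -2, -2, -2 | 0 | 0 | -2, -2, -2 |
| -2, -2, -2 | 0.5 | 0 | -2, -3, -3.5 |
| -2, -2, -2 | 1 | 0 | -2, -4, -6 |
| -2, -2, -2 | 0 | -1 | -3, -4, -5 |
| -1, -3, 0 | 0.5 | 0 | -1, -3.5, -1.75 |
| -1, -3, 0 | 1 | 0 | -1, -4, -4 |

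For example, at r = 0.5 with equal effects, C_3 = 0.25·(-2) + 0.5·(-2) + (-2) = -3.5.

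**Would subtraction recover the yearly effects?** C_2 − C_1 = t + (r − 1)·e_1 + e_2. With full persistence and no trend this is e_2. With half persistence and equal effects of -2 it is -3 − (-2) = -1, and C_3 − C_2 = -3.5 − (-3) = -0.5, although each year's own effect is -2. Adjacent differences remove full carry-over but still mix the new target with fading earlier effects, and with trend where there is one.

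**Award share.** Statistical analysis says the share changed with each year's guideline. The Introduction gives 10% from 2016/17 onward. On the Introduction's figures, 2016/17 and 2017/18 offer no difference in share to compare, and any change between 2015/16 and 2016/17 coincides with the move from 1% to 4%. On the other statement, share and target change together every year. On neither reading can the share effect be isolated.

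**Other parts of the plan.** The interrupted time series has a single break, at March 2015. The shifted-date sensitivity analyses address anticipation and lag. The binary target-achievement outcome records attainment, not what a target caused. Limitations covers ignorability and unmeasured confounding in general terms. None of these separates a year's guidance from the QP years before it.

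**The case against.** The strongest defence is that a common baseline suits the way the target is set. The 1% target is defined against a fixed 2013/14 mean, and the 4% target reads naturally as a tightening on the same scale: 1.61 × 0.99 = 1.594, then 1.61 × 0.96 = 1.546 items per STAR-PU, a further step of 0.048. On that reading, total change since the pre-QP year is a legitimate quantity. This stands. It supports the contrasts as cumulative effects, but not the sentence that turns them into a comparison of targets.

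A reader might go further than the article allows in five ways.

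- That all three contrasts carry earlier QP years. The 2015/16 contrast has none, although a secular trend would still affect it.
- That a later target would necessarily be credited with the whole earlier effect. This happens only if each contrast is read alone. With own effects of -6, 0, 0 and full persistence the contrasts are -6, -6, -6, and setting them side by side shows no further fall.
- That the later contrasts are simply the sum of the yearly effects. That requires full persistence, for which the article gives no figure. It does ask whether effects are sustained in the long term, so carry-over cannot be assumed away.
- That the award share is known to have been constant from 2016/17. The article also says that it changed each year.
- That the study's main aim or its policy conclusions depend on this comparison. The aim is the direct, indirect and total effects of QP, and the Discussion rests future revisions on the before-after comparison and the strategies that explain it. The target comparison is secondary.

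**Conclusion.** The article states a property that the design does not have. The three contrasts estimate change since the pre-QP year after one, two and three years of QP. The second and third do not isolate the effect of that year's target or award share. The distortion depends on unknown persistence and trend: with equal yearly effects of -2% and no trend, the third contrast is -2% under no persistence, -3.5% under half and -6% under full. These values are illustrative, not estimates. The conclusion itself needs only that some earlier effect persists or that some trend exists. The planned contrasts stay usable. What must change is the inference drawn from them, and that changes what the study can conclude about targets and incentives.

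**What to change.** 1. Define the three contrasts as cumulative effects after one, two and three years of QP, and name the control year.
2. Withdraw the claim that they compare the effects of target levels or award shares. State that target level, award share, years of exposure and calendar year cannot be separated in this design.
3. Optionally, report adjacent-year differences in prescribing rate (2016/17 against 2015/16, and 2017/18 against 2016/17) as descriptive increments with the same caveat. Extend them to mediation only if mediator data vary between post-QP years. The article describes one survey of CCG leads plus unspecified other sources and does not say that they do.
4. Reconcile Statistical analysis, where the award share changes each year, with the Introduction, where it is 10% from 2016/17 on.

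Items 1, 2 and 4 are wording. Item 3 needs little more than subtraction for the prescribing rates, but the increments will be less precise relative to their size. The real cost is giving up a secondary claim.

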**Figure 1 F1:**
[figure not shown]
Conceptual model. The direct effect is represented by the path between the QP initiative (predictor) and antibiotic prescribing rate (outcome). *Not directly observed within our data. AMS, antimicrobial stewardship; CCG, Clinical Commissioning Group; CMO, Chief Medical Officer; QP, Quality Premium; TARGET, Treat Antibiotics Responsibly, Guidance, Education, Tools.

Our conceptual model suggests that in addition to its direct impact, the QP initiative acts by stimulating and enhancing the adoption of existing strategies to reduce and optimise antibiotic prescribing. In investigating the potential pathways connecting QP to reductions in antibiotic prescribing, we will be examining the hypothesis that factors like the Chief Medical Officer’s (CMO) letter, Treat Antibiotics Responsibly, Guidance, Education, Tools (TARGET) toolkit, antibiotic auditing, benchmarking, local incentives at CCG level, prescribers and patients’ antimicrobial stewardship (AMS) education/training can transmit part of the influence of the QP initiative to antibiotic prescribing.

First implemented in September 2014, the CMO letter, which provided social norm feedback to primary care practitioners in England whose antibiotic prescribing rate was in the top 20%, reduced antibiotic prescribing by 3.3% in 6 months in a randomised trial.^26^ The criteria for selecting practices that received the letters in the subsequent years changed with the addition of measures like a change in antibiotic prescribing over time and whether practices have previously been sent CMO letter.

Another important mediator hypothesised in our conceptual model is AMS education/training of prescribers and patients. Educating and training prescribers on the importance of antibiotic stewardship and ways to promote prudence can help prescribers make better decisions on when an antibiotic is indicated and can also improve patients’ knowledge on the appropriate use of antibiotics. AMS interventions targeted at patients can improve their knowledge of when antibiotics are not needed and increase confidence and skills on how to self-care, which can result in reduced consultations for self-limiting illness and thus reduced antibiotic prescriptions.

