Using a unified model for the natural direct and indirect effects,^31^ we will investigate the relationship between the QP initiative, the potential mediators and antibiotic prescribing rate with adjustment for the practice and CCG characteristics. This approach addresses the issues associated with the traditional approach to mediation analysis that obtains natural direct and indirect effect estimates through a non-trivial combination of parameter estimates from multiple models for the regression of the mediator and that of the outcome.^32 43^ Also, the unified model is applicable to nonlinear regressions, different measurement types for outcome and mediator variables, and allows for interaction between the exposure and the mediator.^31^

We will first fit single-mediator models with each mediator separately modelled using the *medeff* function in Stata.^44^ With the single-mediator models, we will be able to establish the individual influence of each potential-mediator variable. Variables that showed a mediating effect in the single-mediator models will be added to build a multiple-mediator model using a sequential mediation analysis method.^45^

A sequential multiple-mediator analysis is preferred to merely summing the effects of the single mediators because the sum may differ from the joint mediated effect, particularly as our potential mediators may influence one another.^45^ Modelling all the significant mediators together provides a more accurate assessment of the mediation effects and causal relationship,^46 47^ while assessing the indirect effect of a group of mediators in explaining how and why the intervention impacts on the outcome. The ordering of the mediators in the sequential mediation analysis will be based on evidence from the literature and the outcome of our stakeholders’ workshop designed to identify possible pathways between the predictor, mediators and outcome. The workshop that will validate our conceptual model will also enable us to identify what mediators affect one another and inform interactions to include in our model. All analysis will be conducted in the Stata statistical package V.15.1.

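### Significance in single-mediator models decides entry to the joint mediation model, so the screen can admit mediators with no effect of their own and, in some settings, drop real ones

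*Protocol article*

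**What the plan says.** All of this is in the protocol article, mainly under Statistical analysis.

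- **Entry rule.** Each mediator is first fitted alone with the Stata *medeff* function. Then: "Variables that showed a mediating effect in the single-mediator models will be added to build a multiple-mediator model".
- **Criterion.** No level, interval or effect size is given. The next paragraph indicates that statistical significance is meant: "Modelling all the significant mediators together provides a more accurate assessment of the mediation effects and causal relationship".
- **Reason for the joint model.** Summing single-mediator effects is rejected because "the sum may differ from the joint mediated effect, particularly as our potential mediators may influence one another".
- **Reading of the single-mediator results.** "With the single-mediator models, we will be able to establish the individual influence of each potential-mediator variable".
- **Role of the workshop.** Together with the literature it sets the ordering of mediators. It will also "enable us to identify what mediators affect one another and inform interactions to include in our model". It is not said to decide which mediators enter.
- **Candidates.** The text under Figure 1 names the CMO letter and then "Tools (TARGET) toolkit, antibiotic auditing, benchmarking, local incentives at CCG level, prescribers and patients", the last two referring to stewardship education or training. That makes about seven, or six to eight depending on how they are counted. The figure legend marks some elements of the model as not observed in the data.
- **Sensitivity analyses.** The section lists dummy implementation dates, a binary outcome and practice subgroups. It lists no joint model of all mediators.

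**The concern.** The article calls the joint model more accurate, yet a less accurate step decides what that model may contain.

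Suppose one strategy prompts another, or both follow from the same CCG-level effort. The single-mediator model for the downstream or correlated strategy then leaves out a variable that affects both that strategy and prescribing. Its estimated indirect effect takes on part of the other strategy's effect, and the screen acts on that estimate.

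Such overlap is plausible from the article itself. The Introduction describes TARGET as containing audit tools, training resources and patient leaflets, while auditing and prescriber and patient education are listed as separate mediators.

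The study's question is which strategies carry the QP effect. A mediator wrongly admitted will already have been described as having an individual influence, although the joint model may later show none. A mediator wrongly dropped cannot be recovered, and the joint indirect effect omits its path.

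**Working it through.** **Inputs from the article.** 187 of 209 CCGs have mediator data (Variables). There are three post-QP years, each compared with the year before QP (Statistical analysis), and about seven candidate mediators. The article gives no alpha, effect size or power figure for the mediation step, so there is no figure of its own to reproduce.

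**Assumptions for the simulation.** 187 CCGs before and 187 after QP, treated as independent; two continuous mediators with residual SD 1; QP-to-mediator path a = 0.5; outcome residual SD 1; 2,000 runs per setting. The indirect effect is tested with a Monte Carlo 95% interval, once with the mediator alone (the screen) and once with both mediators in the outcome regression (joint). Let b1 and b2 be the mediator-to-outcome paths and rho the residual correlation between mediators.

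**Formula.** Fitted alone, mediator 2 has expected slope b2 + rho × b1, so its apparent indirect effect is a × (b2 + rho × b1). The correct value in this set-up is a × b2.

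**1. Null mediator correlated with a real one (b1 = −0.3, b2 = 0; true indirect effect 0).**

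| rho | Apparent effect, 0.5 × rho × (−0.3) | Passes screen | Flagged jointly |
|---|---|---|---|
| 0 | 0 | 5% | 6% |
| 0.3 | −0.045 | 33% | 5% |
| 0.5 | −0.075 | 77% | 4% |
| 0.7 | −0.105 | 97% | 4% |

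A separate simulation, also with assumed paths, gave 40% to 79% for correlations of 0.3 to 0.5, against 4% jointly. In the same work, a null mediator lying downstream of a real one passed in 67% of runs, against 6% jointly.

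**2. Real mediator with an offsetting relation (b1 = −0.2, b2 = −0.3; true indirect effect of mediator 1 = 0.5 × (−0.2) = −0.10).** Its apparent effect alone is 0.5 × (−0.2 + rho × (−0.3)).

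| rho | Apparent effect | Passes screen | Detected jointly |
|---|---|---|---|
| 0 | −0.10 | 94% | 96% |
| −0.3 | −0.055 | 49% | 95% |
| −0.5 | −0.025 | 13% | 90% |
| −0.67 | about 0 | 5% | 78% |

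A positive correlation with a mediator of opposite sign gives nearly the same pass rates (95%, 47%, 13%, 5%).

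**3. Real mediators positively correlated and acting in the same direction** (rho 0.3 to 0.5, paths −0.2 and −0.3). The screen kept each in over 99% of runs.

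**4. Upstream mediator acting wholly through a downstream one** (QP to M1 0.5, M1 to M2 0.5, M2 to outcome −0.3). M1's true indirect effect is 0.5 × 0.5 × (−0.3) = −0.075. Its single-mediator model recovers this without bias and passes it in 80% of runs. A regression with both mediators and no ordering flags M1 in only 5%.

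**5. Multiplicity alone**, with independent null tests at an assumed 5%. For seven mediators in one year, 1 − 0.95^7 = 30.2%. Over three years, 1 − 0.95^21 = 65.9%. With six or eight mediators the three-year figures are 60.3% and 70.8%. These are upper illustrations: the years share one control year, and where neither path of a mediator exists, the indirect-effect test passed in only 0.1% to 0.2% of runs.

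**The case against.** The strongest reply has five parts.

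- **Influence is only a possibility and has a direction.** The article says "particularly as our potential mediators may influence one another". A reader might infer that every single-mediator model is therefore biased. The document does not support that: a mediator upstream of the others is not confounded by them (check 4). This stands, and it limits the point to downstream or correlated mediators. It also means that an unordered regression is not the planned sequential analysis, so the joint percentages are a benchmark for correlated or downstream mediators only.
- **Dropping a real mediator needs special conditions.** The conceptual model has QP stimulating strategies together, which suggests positive association, and check 3 then shows almost no loss. This also stands: dropping needs offsetting relations or low power.
- **The joint model looks again at whatever is admitted.** This is partly right. It can correct a false admission, but not an omission, and not the claim of individual influence already made.
- **The threshold and multiplicity control belong in a fuller plan.** That is fair for the threshold. The entry rule itself is fixed in the article, and a threshold would not remove it.
- **The Limitations section already concedes sequential ignorability and unmeasured confounding.** It does, but the issue here is confounding by measured mediators, which the authors can address with data they hold.

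Two further inferences go too far. A 66% chance of a false entry assumes 21 independent null tests at a level that the article never states. The article also does not say that selection is repeated by year, and total effects do not depend on the mediator set, so it cannot be said that the yearly results would not be comparable.

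**Conclusion.** The point holds in conditional form. The entry rule conflicts with the article's own reason for preferring the joint model, and no listed analysis shows what the rule left out.

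The main risk is false admission. At a correlation of 0.3 to 0.5 with a real mediator, a null mediator passes the screen in roughly 33% to 79% of runs, against about 4% to 6% jointly. Loss of a real mediator is a narrower risk, but one that cannot be reversed. With no correlation, what remains is multiplicity and ordinary power loss.

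Every effect size and correlation here is assumed. Actual mediators may be binary, and the before and after data are paired by CCG, so the percentages show direction and order of magnitude only.

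**What to change.** Enter in the sequential model every mediator that is observed in the data and prespecified by the conceptual model and the workshop, whatever its single-mediator result. Use the same set, in the workshop's ordering, for all three yearly comparisons, and report intervals for all of them. Describe the single-mediator models as descriptive. Elements that Figure 1 marks as not observed cannot be entered and should be named as such.

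If the screen is kept, state its criterion and add the model with all observed mediators as a sensitivity analysis.

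The cost is a change of wording, wider intervals where strategies are correlated across CCGs, and the need for the workshop to order all the candidates. About seven mediators in 187 CCGs is not a number that forces screening.
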